### Procedure

#### Recruitment

The GP and therapists will send in patients suitable to include. See the flow chart in figure 2. The GP and therapists inform the patient about the aim of the study and present an information brochure. If the patient is willing to participate in the study, the GP or therapist contacts the local research assistant (LRA).

**Figure 2 F2:**
[figure not shown]
**NECKproject flow chart**.

The LRA schedules an appointment with the patient. The patient will be informed again by the LRA about the contents and objectives of the study. After this, the LRA conducts a diagnostic examination according to protocol. Training and an instructional DVD is provided by the NECKprojectgroup to the LRA to ensure a correct intake procedure.

The purpose of the intake procedure is to assess inclusion and exclusion criteria. Should the patient be eligible, he/she is informed about how to fill in the questionnaires either digitally or on paper. After signing the informed consent, randomisation takes place. The patient receives an envelope with the name and address of the (local) therapist that will provide the treatment. The patient makes an appointment with the therapist in attendance and starts treatment. The LRA has no further contact with the patient in relation to this trial.

All questionnaires are sent either digitally or by mail to the central blinded investigator.

#### Randomisation, blinding and allocation

Block randomisation will take place through the computer after pre-stratification on the basis of prognostic aspects for the complaints: level score of the main complaint (scale 10: <7 or ≥ 7) and age (< 40 or ≥ 40 years) [59,60].

Four groups are formed which are randomized for both intervention groups. The randomisation scheme will be generated by the central computer. The LRA is blinded for the randomisation.

Treatment with physical therapy and MTU will take place at different locations. The investigator in charge of the database has no access to the key of the combination patient data - research number - treatment allocation. In the case of missing data the computer system will automatically generate an email to the participant directly or to the secretary of the NECKprojectgroup. The computer or secretary will send the patient a standard reminder. None of the therapists know the patient number(s).

The data from the questionnaires filled in digitally on http://www.neckproject.nl are sent directly to the database of the central researcher. The researcher is blinded from patients' data and type of intervention. The questionnaires filled in by hand are sent to a central freepost address. These lists are entered into the database by a secretary. Loss of data should be prevented by actively reminding the patient by email, mail or telephone.

Patients who fill in the forms digitally will automatically receive a reminder by email. Patients who fill in the lists by hand will receive them through the post. The secretary will attend to this.

Each treatment sessions will be registered by using standard forms filled in by the therapist. By doing spot checks the information received about the content of the treatment session will be inspected by the researcher from the UMC St Radboud.

Visitations will take place to ensure the therapists in attendance are keeping to the research protocols.

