## Background

Neck pain is one of the most common complaints of the musculoskeletal system.

Approximately two thirds of the population will at some point in their life experience neck pain [1]. Prevalence rises with age in both sexes and is highest at ages between 50 and 59. In general women suffer from neck complaints twice as often as men.

Prevalence of neck complaints is between 10% and 15% [2]. In the Netherlands, the point prevalence in absolute figures, calculated in the year 2000, amounted to 594,000 males and 1,013,700 females registered with chronic neck complaints [3]. Systematic reviews showed a considerable heterogeneity in prevalence of neck complains. Fejer et al found a range of the one-month prevalence from 15.4% to 41% [4]. Hogg-Johnson found a range from 15.4% to 45.3% among adults, interfering with activities ranged from 7.5% to 41.5% [5]. Bot showed an incidence of 23.1 per 1000 person-years of neck symptoms in a Dutch national survey of general practice [6].

The total costs related to neck pain in the Netherlands added up to approximately 668 million Euros in 1996. Direct medical costs amounted to 160 million Euros (23% of the total costs related to neck complaints) [2]. Allied health care (such as occupational therapy and physical therapy) made up the largest proportion of the direct costs (84%) [2]. As such, neck pain forms a significant personal and economical problem.

Neck pain can be caused by traumata (specifically traffic accidents), infections, tumours, congenital defects and inflammations; however in many cases it is not possible to determine the underlying cause. In these cases neck pain will be regarded as 'non-specific neck pain'.

In case of acute neck pain the general practitioner (GP) will usually not take immediate action. Pain medication might be prescribed [7]. Research by Vos indicates that 51% of patients having neck pain are referred to physical therapy or manual therapy [7].

These figures may differ internationally because of different referral policy.

If the complaints are persistent (for six months or longer) it appears that the average discomfort perceived will remain fairly stable [8]. It is clinically and economically relevant to ensure that patients do not end up in this chronic phase.

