### Trial Objectives

The primary objective is to compare the short-term effectiveness (7 weeks) and long-term effectiveness (52 weeks) of MTU with physical therapy in patients with sub-acute and chronic neck pain with regard to global perceived effect, functioning and pain.

The cost-effectiveness of manual therapy compared with physiotherapy will also be evaluated.

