### Inclusion and exclusion

Males and females aged between 18 and 70 years having neck pain for at least two weeks and with the last episode started at maximum of 52 weeks ago are eligible. Neck pain is the primary pain at the time of inclusion and must be provoked and reproduced as mechanical neck pain by movement or posture of the neck. Participants may have cervicogenic headache and radiation to the elbow. Exclusion criteria are: presence of red flags such as specific neck pain caused by cervical radiculopathy, entrapment neuropathy, myelopathy, unexplained fever, unexplained weight loss, nocturnal persistent pain, general malaise [33]; surgery of the cervical spine; pregnancy; whiplash trauma (in the past or recent, as cause of the complaint); physical conditions seriously impeding treatment (such as amputations, being wheelchair bound, illness); insufficient knowledge and command of the Dutch language for answering the questionnaires (to be judged by the research assistant); therapeutic treatment for neck pain in the previous three months such as physical therapy, manual therapy, osteopathy, chiropractics and acupuncture.

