### Statistics

#### Descriptive statistics

Demographic data (gender, average age, disability/fitness, duration of complaints, headache of cervical origin, use of medication and other items) will be presented.

Outcomes will be presented per group (baseline, MTU, physical therapy) in mean, standard deviation and 95% confidence interval.

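### Complaint duration is treated as prognostic and known before randomisation, but the named arm comparisons of GPE and NDI do not use it: a modest, avoidable loss of precision

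*Protocol article*

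**What the plan says.** - **Entry range** (Inclusion and exclusion): adults "having neck pain for at least two weeks and with the last episode started at maximum of 52 weeks ago are eligible". Duration must therefore be established at intake, which the Recruitment section places before randomisation.
- **Prognosis** (Background): "If the complaints are persistent (for six months or longer) it appears that the average discomfort perceived will remain fairly stable".
- **Objective** (Trial Objectives): one comparison of "MTU with physical therapy in patients with sub-acute and chronic neck pain".
- **Allocation** (Randomisation, blinding and allocation): "Block randomisation will take place through the computer after pre-stratification on the basis of prognostic aspects for the complaints". The factors are the main-complaint score (cut at 7) and age (cut at 40), which make four strata.
- **Use of duration** (Descriptive statistics): "Demographic data (gender, average age, disability/fitness, duration of complaints, headache of cervical origin, use of medication and other items) will be presented". This is the only place in the Statistics section that names duration.
- **Arm comparisons** (Multi-variate analysis): ANOVA or a mixed model for continuous outcomes and a Chi-Square test for dichotomous ones, with no covariate named. GPE may be split into responders and non-responders. A separate regression is to examine how baseline variables influence the outcomes; it names neither the variables nor a treatment term.

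**The concern.** The protocol selects its stratification factors because they are prognostic, and its own Background describes duration in the same terms, with a boundary that falls inside the entry range. Duration is on file for every patient at no extra cost, yet no named arm comparison uses it.

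This matters most for GPE. It is the outcome that set the sample size, and Table 1 shows no baseline GPE, so the outcome's own starting value cannot absorb variation between patients. If response is tested with a plain Chi-Square, all variation due to duration stays in the error term, and a chance difference between the arms in the share of long-standing complaints passes straight into the estimate. At stake is the width of the interval, and an argument after the fact about adjustment should the planned baseline comparison show such a difference.

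**Working it through.** **The plan's own figures.** Sample size gives 76 per group, 15% drop-out and 90 per group recruited. 76 / (1 − 0.15) = 89.4, so 90 is reproduced. The comparator rate and the sidedness behind 76 are not stated. Two-sided with continuity correction, 68.3% against 88.3% gives 76; one-sided without correction, 68.3% against 48.3% gives 75. Nothing below depends on which was used, except the power figures, whose basis is given there.

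**Assumptions.** The protocol gives neither the share q of patients with six months or more of complaints nor the recovery gap d between the duration groups. Main case: q = 50%, d = 20 to 30 points, overall recovery 60%. Wider range: q = 20% to 50%, d = 10 to 30 points.

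**1. Chance imbalance, 90 per arm**
- SD of the between-arm difference in q = sqrt(2 × 0.5 × 0.5 / 90) = 0.0745.
- P(|difference| > 0.10) = 2 × [1 − Φ(0.10 / 0.0745)] = 0.18.

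**2. Shift in the GPE difference from a 10-point imbalance**
- Shift = imbalance × d: 0.10 × 0.20 = 2 points; 0.10 × 0.30 = 3 points.
- SE of the GPE difference = sqrt(2 × 0.24 / 90) = 0.073, or 7.3 points.
- The shift is therefore 2 / 7.3 = 0.27 to 3 / 7.3 = 0.41 of one standard error.
- Wider range: the 95% limit of imbalance is 11.7 points (q = 20%) to 14.6 points (q = 50%). The shift at that limit is 0.117 × 10 = 1.2 to 0.146 × 30 = 4.4 points, against a 20-point target.

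**3. Variance explained by duration (q = 50%)**
- Recovery 70% against 50%: 0.10² / 0.24 = 4.2%.
- Recovery 75% against 45%: 0.15² / 0.24 = 9.4%.
- As patients: 180 × 0.042 = 7.5 and 180 × 0.094 = 16.9, so roughly 7 to 17 of 180.

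Steps 2 and 3 measure the same loss. The SD of the shift is 0.0745 × 0.20 = 0.0149 to 0.0745 × 0.30 = 0.0224. Squared and divided by 0.073², this gives the same 4.2% and 9.4%. The two should not be added together.

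**4. Power gained by adjustment** (76 analysed per arm, 68.3% against 48.3%, two-sided 0.05, q = 30% to 50%)
- Unadjusted variance sum: 0.683 × 0.317 + 0.483 × 0.517 = 0.4662. Power = Φ(0.20 / sqrt(0.4662 / 76) − 1.96) = 72.4%.
- Adjusted variance sum = 0.4662 − 2q(1 − q)d². With d = 10 points and q = 30%, the ratio to unadjusted is 0.991 and power is 72.7%. With d = 30 points and q = 50%, the ratio is 0.904 and power is 76.6%.
- The gain is about 0.4 to 4 points of power.

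**5. Separate answers by duration.** A 20-point effect within one duration group has about 27% power at a 30% share (about 23 per arm) and 42% at a 50% share (38 per arm). A 20-point interaction has about 25% power at a 50% share.

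**The case against.** The strongest reply is that nothing here is an error. The objective is a single pooled comparison and a pooled estimate answers it. Randomisation is valid without duration as a factor, and chance imbalance is ordinary sampling variation that the type I error and confidence interval already cover. Severity and age were chosen with cited support that cannot be checked here. Covariate lists are commonly left to an analysis plan, which is not shown. All of that stands. It limits the point to efficiency. The last argument does not remove it, because the article does not merely omit a list: it names a test for dichotomous outcomes that cannot take a covariate.

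A reader might infer more than the documents support:
- **That the comparison is biased.** It is not; see the 2 to 3 points against a standard error of 7.3.
- **That sub-acute and chronic patients need separate answers.** Trial Objectives names them together, and the Background describes the average course of persistent pain, not a treatment effect that changes with duration.
- **That duration enters no treatment comparison at all.** The planned regression on baseline variables may include it, perhaps alongside treatment; the text does not say.
- **That duration is nearly the only prognostic measure for GPE.** Baseline NDI, pain score, severity and age are all available.
- **That duration should become a third randomisation factor.** Recruitment began in September 2008 (Discussion), so this would change the scheme mid-trial and make eight strata of about 22 patients. It is a debatable trade for so small a gain.

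**Conclusion.** The point holds as a minor matter of precision. The protocol treats duration as prognostic and holds it for every patient, but the arm comparisons it names leave it out. If half the patients have long-standing complaints and the recovery gap is 20 to 30 points, 4% to 9% of GPE variance goes unused. Over the wider assumed range the gain from adjustment is about 0.4 to 4 points of power. With a smaller gap or a smaller long-duration share, the gain approaches nothing. The share and the gap are assumptions; the documents give neither.

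**What to change.** Before unblinding, pre-specify the following:
- **GPE response:** replace the plain Chi-Square with a covariate-adjusted model containing treatment, baseline duration and the two stratification factors (severity and age). Report the adjusted risk difference with 95% CI, for example by standardising a logistic model over the trial population, so that the result stays on the scale of the 20-point target.
- **NDI:** use the same covariates plus baseline NDI in the ANOVA or mixed model.
- **Form of duration:** fix it in advance, either as weeks or split at the six-month boundary in the Background.
- **Estimates by duration group:** label any that are shown as exploratory.

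Leave the randomisation scheme unchanged. The cost is slightly more analysis work and some dependence on a model. No new data are needed, and the adjustment covers all patients, including those already randomised.

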#### Side effects

All side-effects, both reported spontaneously by patients and noticed by the therapist, are registered. Any serious side-effects are registered and reported to the Medical Ethic Commission in charge, according to the rules of this organisation.

### Statistics

#### Descriptive statistics

Demographic data (gender, average age, disability/fitness, duration of complaints, headache of cervical origin, use of medication and other items) will be presented.

Outcomes will be presented per group (baseline, MTU, physical therapy) in mean, standard deviation and 95% confidence interval.

#### Multi-variate analysis

An ANOVA will be used to analyze differences between conditions per person (within subject) and per group (between groups).

Descriptive statistics will be applied to make a comparison between the baseline data of the manual therapy and the physical therapy groups and to assess whether the randomisation has been successful. Group differences between the interventions with a 95% confidence interval will be calculated for all outcome measures.

The statistical analyses will be carried out according to the intention-to-treat principle, whereby the patients are analysed in the intervention group in which they were originally placed. The differences between groups will be tested by ANOVA/mixed model (continuously) and by the Chi-Square test for dichotomous variables.

Multi-variate regression analysis will be used to test the influence of the baseline variables on the outcomes.

For the primary outcome measure Global Perceived Effect (GPE) a selection can be made between responders (positive effect) and non-responders (no or negative effect) to the treatment received.

The data will be processed by SPSS/SAS statistical software.

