### Sample size

The sample size is based on one of the two primary outcome variables, Neck Disability Index (NDI) and Global Perceived Effect (GPE). The GPE is chosen, because this outcome variable needs the largest group of participants. Previous studies have shown that the effect of manual therapy on GPE is 68.3% [13] and 70.1% [18].

A 20% difference on the GPE scale is considered clinically relevant. Based on α = .05 and an 80% power (β = 0.2) 76 participants per intervention group are required.

With regard to prospective drop outs (15%), 90 participants per group will be recruited in this trial. A similar sample size was used in previous research [19,34,35].

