#### Secondary outcomes

To assess neck pain intensity the Numeric Rating Scale (NRS) will be used. This scale (11 points) measures the pain intensity experienced by the patient in the previous week. Dalton et al argued for standardization of pain measuring by means of the 11-point Numeric Rating Scale (NRS) [45]. The Visual Analogue Scale (VAS) and the NRS are the most cited pain measures, largely because they are simple to use. The NRS is a sensitive instrument, comparable with the VAS [46,47] or more sensitive than the VAS [48]. The NRS has been chosen on the basis of administrative aspects rather than for statistical power. It has been proved to be more comprehensible for patients [45-47,49,50]. Also the NRS is valid for verbal patient questioning [51].

The general health questionnaire (SF36) will be used to put together a detailed health profile on the basis of scores on eight health dimensions as well as a sum score on both physical and mental health [52].

The EuroQol5D is a standardized, non-disease-specific instrument for describing and valuing health states. It has the additional possibility of converting the descriptive data into values for economic (cost-effectiveness) analysis by linking patients' health state descriptions to empirical valuations of health states obtained from the general population [53]. EuroQol5D is simple to use, valid, responsive to change and reliable instrument for group comparisons [54-56]. The EuroQol5D is a two-part instrument. Part one records self-reported problems on each of five 'domains': mobility, self-care, usual activities, pain/discomfort and anxiety/depression. Each domain is divided into three levels of severity corresponding to no problem, some problem and extreme problem. Part two of the questionnaire records the subject's self-assessed VAS rating of health.

Participants are to fill in questions about (partial) disablement/return to work (if applicable), use of analgesic (types of and quantities), medical consultation during treatment and follow/up, costs and side effects [57,58].

The patient will fill in the questionnaires at baseline, 3, 7, 13, 26, 39 and 52 weeks after treatment has started (see table 1).

**Table 1 T1:** Timing of measurements

measurements	Baseline T0	T3	T7	T13	T26	T39	T52
In- and exclusion	X						

Demographic data	X						

GPE		X	X	X	X		X

NDI-DV	X	X	X	X	X		X

NRS pain	X	X	X	X	X		X

SF-36	X		X				X

Side effect		X	X	X			

EuroQol5D		X	X	X	X	X	X

Costs		X	X	X	X	X	X

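### The plan leaves NDI-DV and NRS pain open between ANOVA and a mixed model; the classical repeated-measures ANOVA would delete every patient missing one form

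*Protocol article*

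**What the plan says.** Under Statistics, the Multi-variate analysis section opens with an unconditional commitment: "An ANOVA will be used to analyze differences between conditions per person (within subject) and per group (between groups". Two paragraphs later, between-group differences in continuous outcomes are assigned to ANOVA or a mixed model, with the two names joined by a slash. Dichotomous outcomes are assigned to a chi-square test. Nothing says which of the two continuous methods is primary, or which visits enter the within-subject factor.

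On the analysis population the section says: "The statistical analyses will be carried out according to the intention-to-treat principle, whereby the patients are analysed in the intervention group" of original placement. It adds nothing about missing forms.

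On the schedule, the Secondary outcomes section says: "The patient will fill in the questionnaires at baseline, 3, 7, 13, 26, 39 and 52 weeks after treatment has started". Table 1 narrows this by instrument. NDI-DV (a primary outcome) and NRS pain (secondary) are collected at baseline and at 3, 7, 13, 26 and 52 weeks, with none at 39 weeks. That is six forms, five of them after baseline. Trial Objectives names 7 and 52 weeks as the short-term and long-term time points.

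On expected loss, the Sample size section says: "With regard to prospective drop outs (15%), 90 participants per group will be recruited in this trial".

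**The concern.** The two methods treat an incomplete patient differently. A classical repeated-measures ANOVA needs a full row of visits, so one skipped form removes the patient and all the forms that patient did return. A likelihood-based mixed model uses whatever visits are present. The two can therefore analyse different patients, rest on different missing-data assumptions and give different estimates.

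Three things are at stake for NDI-DV and NRS.

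- **Bias.** Outcomes are self-reported on web or postal forms over 52 weeks, and patients know who treats them, because the envelope names the therapist. It is plausible, though not shown, that recovered or dissatisfied patients return fewer forms. Complete-case ANOVA has no protection against this. A mixed model has some, as far as the observed forms predict the missing ones.
- **Waste.** Forms already collected at 3 to 26 weeks are thrown away.
- **An open choice.** With two methods named and neither primary, the choice can be made after the results of both are known.

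**Working it through.** **Inputs from the protocol article.** 76 per group required, 15% dropout and 90 per group recruited (Sample size); five NDI-DV and NRS forms after baseline (Table 1). **Assumed:** the rate m at which patients who do not drop out skip a form. The article gives no such rate, so a range of 1% to 5% is shown. Skips are taken as independent between visits and the baseline form as complete.

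**Step 1, the plan's own figure.** 76 / (1 − 0.15) = 89.4, rounded up to 90. The inflation reproduces. In the other direction, 90 × 0.85 = 76.5 per arm remain after the planned dropout.

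**Step 2, complete cases under listwise deletion.** Dropout is charged to one follow-up. The remaining patients may skip a form at any of the other four, so complete cases per arm = 90 × 0.85 × (1 − m)^4.

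- m = 0%: 76.5
- m = 1%: 76.5 × 0.99^4 = 73.5
- m = 2%: 76.5 × 0.98^4 = 70.6
- m = 3%: 76.5 × 0.97^4 = 67.7
- m = 5%: 76.5 × 0.95^4 = 62.3

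Patients deleted although they did not drop out: 76.5 − 73.5 = 3.0 per arm at 1%, and 76.5 − 62.3 = 14.2 per arm at 5%.

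**Step 3, without separate dropout.** If each of the five follow-up forms is simply missed independently by 5% of patients, 0.95^5 = 0.774 are complete, and 90 × 0.774 = 69.6 per arm. A patient would be without any follow-up with probability 0.05^5, which is negligible, so a mixed model would keep practically all 90.

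**Step 4, what this does to precision.** For a plain two-group comparison of means (two-sided 5%, 80% power), the detectable standardized difference is (1.960 + 0.842) × √(2/n). It is 0.45 at n = 76.5, 0.46 at n = 73.5 and 0.50 at n = 62.3. The loss of precision is modest. The possible bias and the open choice of method weigh more.

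**The case against.** The strongest reply is that the mixed model is already in the plan, so deletion happens only if the other option is taken. That is right, and the point is conditional for this reason. It does not remove the point: the section's opening sentence commits to ANOVA without condition, and the later slash does not withdraw it.

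A second reply is that the section never says that all visits enter the within-subject factor. An ANOVA of baseline against 7 weeks alone would lose only patients without one of those two forms, which is close to the loss that the 15% covers. The active reminders planned under Randomisation, blinding and allocation should also keep skip rates low. Both replies stand as limits on the counts above, which are illustrations and not forecasts.

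A reader might go further and infer three stronger claims that the documents do not support.

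- **A contradiction with intention to treat.** The article defines that principle by allocated group only. Listwise deletion sits badly with its purpose but does not contradict it as written. A mixed model would also leave out patients with no follow-up form at all.
- **NDI falling below a planned 76.** The 76 belongs to GPE: "The GPE is chosen, because this outcome variable needs the largest group of participants". By that statement NDI needs fewer, and no NDI requirement is given. The only stated loss leaves 76.5.
- **A chi-square on observed GPE only.** The article does not say how a missing GPE is handled. An analysis plan that is not shown may settle it, so silence in a condensed article is no finding.

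**Conclusion.** The point holds in conditional form. The protocol article commits to ANOVA, then lists ANOVA and mixed model side by side for continuous outcomes, and does not fix the primary analysis of NDI-DV and NRS. If the classical repeated-measures ANOVA is run over all six scheduled forms, every patient with a missing form is deleted, and the result is in general unbiased only under missing completely at random.

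The size cannot be fixed from the document. With the stated 15% dropout and an assumed 1% to 5% of forms skipped at each of four other follow-ups, about 73 down to 62 of 90 per arm would be complete. This rests on the assumed rates, on independent skips, and on all visits entering the model. It shows no shortfall against an NDI target, because none is stated. The change is still worth making: one stated option is clearly the weaker, and the better one is already named.

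**What to change.** In the Multi-variate analysis section, remove the ANOVA option for NDI-DV and NRS pain, both in the opening sentence and in the later ANOVA/mixed-model alternative. Name one primary analysis: a mixed model for repeated measures with arm, visit, arm-by-visit interaction and baseline value, using all available follow-up forms at 3, 7, 13, 26 and 52 weeks. Read the between-arm contrasts, with 95% confidence intervals, at 7 and 52 weeks, as in Trial Objectives. State that validity rests on missing at random. Make the change before outcome data are compared by arm.

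The cost is a few sentences of wording. Recruitment, forms and visit schedule do not change, and the model is a standard procedure in the SPSS/SAS software that the article already names.

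### The stated between-group tests are not said to adjust for the stratification factors or for baseline NDI and NRS, and the plain chi-square on GPE responders cannot use the strata; the cost is precision, not false positives.

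*Protocol article*

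**What the plan says.** In the protocol article, the section on randomisation, blinding and allocation states: "Block randomisation will take place through the computer after pre-stratification on the basis of prognostic aspects for the complaints". The factors are "level score of the main complaint (scale 10: <7 or ≥ 7) and age (< 40 or ≥ 40 years"), which gives four strata.

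The outcome section says: "The patient will fill in the questionnaires at baseline, 3, 7, 13, 26, 39 and 52 weeks after treatment has started". Table 1 marks NDI-DV and NRS pain at T0. GPE is marked only from T3 on, since it is a rating of change.

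The Multi-variate analysis section contains four statements that bear on the point:
- The between-group tests: "The differences between groups will be tested by ANOVA/mixed model (continuously) and by the Chi-Square test for dichotomous variables".
- A further ANOVA: "An ANOVA will be used to analyze differences between conditions per person (within subject) and per group (between groups").
- Estimation: "Group differences between the interventions with a 95% confidence interval will be calculated for all outcome measures".
- Baseline variables: "Multi-variate regression analysis will be used to test the influence of the baseline variables on the outcomes".

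The same section allows, but does not require, GPE to be split into responders and non-responders. If it is split, the chi-square is the stated test.

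**The concern.** The design and the analysis do not match. The protocol balances the arms on two factors because it expects them to predict outcome, then names tests that are not said to take them into account. Balancing on a prognostic factor removes its contribution to the between-arm difference. An unadjusted test still counts that contribution as noise, so its standard error is too large. Likewise, the baseline score of a questionnaire is usually a strong predictor of its later score, and the plan does not say how, or whether, it enters the treatment comparison.

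At stake are the width of the intervals and the power for GPE and NDI, at no saving in data collection. There is also an open choice. The section offers an unadjusted test and a regression on baseline variables without saying which one gives the reported treatment effect and its 95% interval.

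**Working it through.** **What the plan gives.** It states no figure for the effect of adjustment. The documents give neither the correlation between baseline and follow-up NDI nor the share of outcome variance explained by the strata. Both are assumed below and shown as ranges.

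**Strata.** Let R² be the share of outcome variance explained by the strata. With allocation balanced within strata, the true variance of the arm difference is (1 − R²) times the variance that an unadjusted analysis uses. Hence:
- actual two-sided type I error = 2 × [1 − Φ(1.96/√(1 − R²))]
- interval width relative to the correct one = 1/√(1 − R²)

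| Assumed R² | Type I error | Width ratio |
|---|---|---|
| 0 | 5.0% | 1.000 |
| 0.05 | 4.4% | 1.026 |
| 0.10 | 3.9% | 1.054 |

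A simulation of stratified block randomisation agrees in direction and size. It used four strata, blocks of four (assumed), 152 patients, a continuous outcome and 4,000 runs per scenario.
- Unadjusted type I error was 5.1%, 4.0% and 3.7% at R² of 0, 0.05 and 0.10. Coverage of the nominal 95% interval was 94.9%, 96.1% and 96.4%.
- With both factors in the model, coverage stayed at 94.9-95.4% in all scenarios.
- Power, unadjusted against adjusted, was 79.9% against 81.4% at R² = 0.05 and 81.6% against 84.4% at R² = 0.10.

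To judge these R² values for a responder outcome, take a response rate of 68.3%, one of the figures in the Sample size section. The total variance is 0.683 × 0.317 = 0.2165. An R² of 0.05 then needs stratum response rates with a standard deviation of √(0.05 × 0.2165) = 0.104, about 10 percentage points. An R² of 0.10 needs √(0.10 × 0.2165) = 0.147, about 15 points. So the assumed range already supposes a clear spread between strata.

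**Baseline NDI.** Let r be the correlation between baseline and follow-up, with equal variance at both times. Relative to a follow-up-only comparison (variance 1):
- change score: 2(1 − r)
- adjustment for baseline as a covariate (ANCOVA): 1 − r²

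| Assumed r | Change score | ANCOVA | Follow-up only ÷ ANCOVA | Change score ÷ ANCOVA |
|---|---|---|---|---|
| 0.4 | 1.20 | 0.84 | 1.19 | 1.43 |
| 0.5 | 1.00 | 0.75 | 1.33 | 1.33 |
| 0.6 | 0.80 | 0.64 | 1.56 | 1.25 |

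The last two columns give the factor by which the sample would have to grow for the less efficient analysis to match ANCOVA. Which column applies depends on whether the ANOVA carries baseline as one of its repeated measures, and the text does not settle that.

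**The case against.** The strongest reply is that silence is not exclusion. The continuous outcomes get an ANOVA or mixed model whose terms are not listed, and a journal article may leave those to the analysis plan. This stands in part. A reader might infer that the tests make no use of baseline NDI at all. The documents do not support that: a within-subject ANOVA or a mixed model may include baseline as a repeated measure, and a suitably specified mixed model can recover the efficiency of ANCOVA. What can be said is that no adjustment is stated. The reply does not cover the chi-square, which is a named test with no place for a covariate. An analysis plan could bring in the strata only by replacing or extending it.

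A second reply is that baseline variables are handled by the planned regression. Its stated aim is their influence on outcome. The text does not say that treatment is left out of that model, but nor does it make that model the source of the treatment effect.

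Third, the error from ignoring the strata is small and on the safe side. That is correct. A reader might take miscalibrated intervals to mean excess false positives; the calculation shows the opposite.

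Finally, a reader might add that the trial is already short of its stated power, so that lost precision is critical. The documents do not support this here. The protocol says: "Based on α = .05 and an 80% power (β = 0.2) 76 participants per intervention group are required", without giving sidedness or the comparator rate. A two-sided calculation with continuity correction for 68.3% against 88.3% gives 76 exactly; one-sided without correction for 68.3% against 48.3% gives 75; two-sided without correction for the same pair gives 95. Whether there is a shortfall depends on which unstated variant was meant. The protocol also says that GPE needs the larger sample, so by its own account NDI is not the limiting outcome.

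**Conclusion.** The point holds as a matter of efficiency and of an unresolved choice of estimate. It does not show bias or inflated type I error.

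- **GPE responders:** the named test cannot use the strata. The effect is mild conservatism whose size rests wholly on the assumed R² of 0.05-0.10. It vanishes if the strata do not predict outcome, and it arises only if the optional responder split is used. The figures come from a general variance argument and a continuous-outcome simulation, so for a binary outcome they are approximate.
- **NDI (and NRS by the same reasoning):** covariate adjustment is not specified. The gain is the larger of the two, but it rests on an assumed correlation of 0.4-0.6 and equal variances. The 25-43% range applies if the plan's ANOVA amounts to a change-score comparison, and the 19-56% range only if baseline is left out. The two ranges must not be combined.

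The change is worth making because it is free and because it fixes in advance which analysis yields the reported effect.

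**What to change.** State the following in the analysis section or the analysis plan, before outcome data are seen by arm:

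1. NDI and NRS: a linear (mixed) model with treatment, the baseline value of the outcome, and both stratification factors as covariates.
2. GPE responders: a Mantel-Haenszel test and risk difference over the four strata; or logistic regression adjusted for the two factors, reported as a standardised risk difference with 95% confidence interval.
3. The treatment effect and its interval are taken from these models. The unadjusted chi-square is kept as a supportive analysis.
4. The regression on baseline variables keeps its stated purpose and is reported separately from the treatment comparison.

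The cost is wording only. The two factors must be known for each patient at randomisation, and Table 1 already schedules NDI-DV and NRS at T0. No patients, visits or data items are added.
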